##### Psychometric measures

In this study, we plan to use both DTSQs and DTSQc. It is common that researcher who wants to evaluate patient satisfaction in different diabetes treatment interventions use DTSQs in its original form (e.g. ‘How satisfied are you with your current treatment?’ Response options: very satisfied to very dissatisfied) [20]. However, surveys who evaluate patient satisfaction tend to produce small variations and most response express positive satisfaction. This leaves small or no rooms to show improved satisfaction later in the trial in respondents who previously scored at or near ceiling. A change version of the DTSQ (DTSQc) was therefore designed to overcome the ceiling effects found with the status version (DTSQs) [21].

The DTSQ encompasses three areas: general treatment satisfaction, hyperglycaemia, and hypoglycaemia. The questionnaire includes eight questions: six about different aspects of treatment satisfaction and two about hyper/hypoglycaemia that has occurred during the last few weeks. Responses are on a 7-point scale. DTSQs scores range from 0 = *very dissatisfied* to 6 = *very satisfied*, and DTSQc scores from ‘+ 3 = *much more satisfied now* to − 3 = *much less satisfied now*, with 0 (midpoint) representing no change’ [22]. The total score is the sum of all points from the questions about different aspects of treatment satisfaction. Therefore, increases in treatment satisfaction produce positive values and decreases in treatment satisfaction negative values, with 0 representing no change. For perceived hyperglycaemia and hypoglycaemia, positive scores indicate an increase in perceived hyperglycaemia or hypoglycaemia, and therefore deterioration in these outcomes [22].

### Check your health

‘Check your Health’ screens perceptions and experiences of physical and emotional health, social relationships, and general quality of life via a vertical thermometer scale. Responses range from 0 to 100, where 0 indicates a perceived very low level of health and quality of life and 100 a very high perceived level of health and quality of life. Using the same scale, a person then reports what they think their physical and emotional health, social relationships and quality of life would be if they did not have diabetes. When the difference is a positive value (e.g. that physical health without diabetes is reported as lower than with diabetes) the burden is interpreted as zero. Check your Health has been tested with both adults and young people with diabetes, and has been shown to have good reliability and validity [23, 24].

### Qualitative interviews

Qualitative interviews will be conducted with approximately 16 individuals. We will perform purposeful sampling with a maximum variation. The interviews will be conducted before and at the end of the intervention and follow a semi-structured interview guide. The interview guide will focus on the following three major topics, Suppl. 2.
Perceptions about virtual care; for example, ‘Do you have any experiences of virtual care’ (before intervention), ‘Which changes do you see the virtual care has brought?’ (after intervention).Hindering and facilitating factors in the context of virtual care; for example, ‘Is it possible to describe some factors or events that may hamper virtual care’ (before intervention) and ‘Which conditions in your daily life have made it difficult or easy to achieve positive outcomes from the virtual care?’ ´Can you describe how you used the application (app) in your daily life and specific aspects of the app that were helpful/not helpful for you´ (after intervention).Problems with virtual care technology; for example, ‘Do you have experience in digital or virtual technology’ (before intervention) and ‘Did you have any problems with the internet or in reaching the diabetes team’ (after intervention).

### Statistical analysis and power calculation

To detect a mean difference of 6 mmol/mol (standard deviation [SD] = 9) in HbA1c, it will be necessary to include at least 37 participants in each group (alpha 0.05, power 80%, two-sided test). Taking dropout rates into consideration, a total of 100 patients will be included in the study. Participants will be randomly assigned to either experimental or control group with a 1:1 distribution as per a computer-generated randomisation.

All analyses will be conducted on an intention-to-treat basis. The difference at the 6-month follow-up between the intervention and wait-list control groups (adjusted for values at baseline) will be analysed with a two-sided independent samples Student’s *t*-test with a 95% confidence interval. A *p*-value < 0.05 will be considered statistically significant. Mean (SD) values and 95% confidence intervals will be used to describe the sample. A secondary analysis of the primary endpoint will adjust for baseline characteristics. For independent samples, a Student’s *t*-test will be used when comparing two categories for interval or ratio data, and a Mann-Whitney U test will be used for ordinal data. When three or more categories are compared, analysis of variance will be used for interval or ratio data and the Kruskal-Wallis test will be used for ordinal data. Generalised estimating equation regression models will be used for comparisons within groups over the three time points. All statistical analyses will be performed with IBM SPSS Statistics.

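### The 6-month HbA1c comparison is described as baseline-adjusted but is assigned to an independent-samples t-test, which cannot adjust; naming ANCOVA resolves the contradiction and gains precision

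*Protocol article*

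**What the plan says.** All the relevant text is in the protocol article, section Statistical analysis and power calculation.

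- **The comparison.** The sentence on the 6-month between-group difference contains the words "wait-list control groups (adjusted for values at baseline) will be analysed with a two-sided independent samples". The test it goes on to name is Student's, reported with a 95% confidence interval.
- **Further adjustment.** "A secondary analysis of the primary endpoint will adjust for baseline characteristics". This is a separate, secondary analysis, and no model is named for it.
- **Other models.** The only regression named is a generalised estimating equation model, and it is reserved for within-group comparisons over time.
- **Sample size.** The calculation takes an HbA1c difference of 6 mmol/mol and an SD of 9, at 80% power and a two-sided alpha of 0.05, and concludes that "it will be necessary to include at least 37 participants in each group". The total is raised to 100 to allow for dropout.

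The Intervention section adds that baseline data are taken in both groups before randomisation, so a baseline HbA1c is available as a covariate.

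**The concern.** The sentence promises a baseline-adjusted difference and names a test that cannot produce one. A two-sample t-test compares two means; baseline can enter only if the outcome itself is redefined, for example as a change score. Subtracting baseline is not the same as adjusting for it. It fixes the coefficient of baseline at 1 instead of estimating it, and so leaves some sensitivity to chance baseline imbalance.

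A reader therefore cannot recover one analysis of the 6-month HbA1c difference from the text. Two t-tests fit the named test, and ANCOVA fits the word adjusted. In any one dataset they can give different estimates, intervals and p-values. The t-test readings also make less use of a baseline measurement that the trial collects anyway.

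**Working it through.** **Inputs.** From the protocol: difference 6 mmol/mol, SD 9, two-sided alpha 0.05, power 80%, 37 per group, 1:1 allocation. Not in the protocol: the correlation r between baseline and 6-month HbA1c. I assume r = 0.5 to 0.8, equal SDs at the two times, and the same r in both groups.

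**Step 1: reproduce the plan's figure.** The normal approximation is n = 2(1.960 + 0.842)² × 9² / 6² = 2 × 7.85 × 2.25 = 35.3, so 36 per group. With the exact noncentral t distribution, power is 79.7% at 36 per group and 80.8% at 37. The stated 37 is therefore correct for a plain two-sample t-test, with no gain from baseline assumed.

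**Step 2: variance under each reading.** With SD σ for a single HbA1c value, the SD that enters the comparison is:

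- t-test on 6-month values: σ
- t-test on change: σ√(2(1 − r))
- ANCOVA: σ√(1 − r²)

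The ANCOVA variance is thus (1 − r²) times that of the raw-value test. Relative to the change-score test it is (1 − r²) / (2(1 − r)) = (1 + r)/2.

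| r | ANCOVA vs raw values | ANCOVA vs change |
|---|---|---|
| 0.5 | 1 − 0.25 = 0.75 (25% smaller) | 0.75 (25% smaller) |
| 0.6 | 1 − 0.36 = 0.64 (36% smaller) | 0.80 (20% smaller) |
| 0.7 | 1 − 0.49 = 0.51 (49% smaller) | 0.85 (15% smaller) |
| 0.8 | 1 − 0.64 = 0.36 (64% smaller) | 0.90 (10% smaller) |

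These ratios do not depend on what the SD of 9 refers to.

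**Step 3: power at 37 per group, taking 9 as the SD of the 6-month value.** Power is from the noncentral t with 72 degrees of freedom and noncentrality 6 / (SD × √(2/37)). The single degree of freedom used by the covariate is ignored.

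| r | Raw values: SD, power | Change: SD, power | ANCOVA: SD, power |
|---|---|---|---|
| 0.5 | 9.00, 80.8% | 9.00, 80.8% | 7.79, 90.4% |
| 0.6 | 9.00, 80.8% | 8.05, 88.5% | 7.20, 94.3% |
| 0.7 | 9.00, 80.8% | 6.97, 95.5% | 6.43, 97.7% |
| 0.8 | 9.00, 80.8% | 5.69, 99.4% | 5.40, 99.7% |

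**Step 4: sensitivity to a lower r.** At r = 0.3, on the same reading of the SD, the change-score test has SD 10.65 and 66.7% power, while ANCOVA has SD 8.59 and 84.3%. The change-score test drops below the raw-value test once r is under 0.5. ANCOVA is at least as precise as either at every r.

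**The case against.** The strongest reply is that the plan can be carried out and is adequately powered. A t-test on change from baseline runs in the named software, uses the baseline values, and in a randomised trial is unbiased with a controlled type I error. The stated 37 per group is right for the named test, and 100 are to be enrolled; with 50 per group analysed, the t-test would have 91.0% power. A valid test that meets its stated power is not an error merely because a more efficient one exists. If ANCOVA was what the authors meant by adjusted, there is no loss at all, only a wrongly named test.

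Most of this stands, and it limits the point. It does not remove the contradiction, because the text neither says that change is the outcome nor names a model that adjusts.

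A reader might infer more than the document supports:

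- **That the analysis cannot be run.** It can; the text is contradictory and underdetermined.
- **That the choice will be made after seeing the data.** Only a journal article is available. A full protocol or SAP may fix the model in advance.
- **That the trial is underpowered.** If 9 were the SD of change and raw 6-month values were tested, power at 37 per group would be 72%, 59% and 43% at r = 0.6, 0.7 and 0.8. That requires 9 to be a change SD, the analyst to disregard the stated adjustment, and r to be well above 0.5. At r = 0.8 it also implies a single-value SD of 9/√0.4 = 14.2, which appears nowhere in the protocol. At r = 0.5 the shortfall vanishes (81%).
- **That the unlabelled SD or the rank test is a further error.** Which quantity the SD of 9 describes is detail that an article may leave out. The statement that "a Mann-Whitney U test will be used for ordinal data" is a general rule, not part of the HbA1c comparison.

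**Conclusion.** The point holds as an internal contradiction in the sentence that defines the 6-month comparison: an adjusted difference is assigned to a test with no covariate. This needs no assumption, and nothing else in the article resolves it. The separate analysis adjusting for baseline characteristics is secondary and has no named model, and the estimating-equation models concern change within groups.

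The cost under either t-test reading is precision forgone, not a sample-size error. Its size depends on the assumed r, and the power gain also depends on taking 9 as the SD of a single 6-month value. Power below 80% at 37 per group is not established. On that reading of the SD it would arise only for a change-score test with r below about 0.5, outside the range assumed here.

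**What to change.** Replace the t-test wording for HbA1c with, for example: *The 6-month HbA1c comparison will use a linear model (ANCOVA) of 6-month HbA1c on randomised group, with baseline HbA1c as a continuous covariate, reporting the adjusted mean difference, its 95% confidence interval and the p-value.* Keep the unadjusted t-test on 6-month values as a sensitivity analysis. It would help to add what the SD of 9 refers to.

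The same model can serve other continuous outcomes measured at baseline, such as time in range, where its assumptions are reasonable. It should not be extended automatically. The Psychometric measures section itself warns of ceiling effects in the status version of the satisfaction questionnaire, and the severe hypoglycaemia and ketoacidosis outcomes listed under Participants and recruitment are events, for which this model is not designed.

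The cost is a sentence or two of protocol or SAP wording. No new data, visits or participants are needed, baseline HbA1c is already collected before randomisation, and the named software fits the model.

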### Intervention

Baseline data will be collected for both groups before randomisation. The intervention group will be offered access to the virtual clinic instantly, and the wait-list control group will be offered the intervention after 6 months. At the 6-month follow-up assessment, a second data collection will be carried out for both groups (intervention and the wait-list groups). The intervention group will then continue with the intervention while the wait-list control group starts the intervention. The third data collection point for both groups will be after 12 months. Finally, data at 18 months will be collected for the wait-list group (after having access to the virtual clinic for 12 months).

Participants who meet the inclusion criteria will be randomly offered the chance to take part in the virtual clinic either immediately or after 6 months. Vista Dialog offers a digital service specially designed to facilitate continuity of care between diabetes patients and their nurses or doctors.

Vista Dialog supports a way of working that allows more frequent communication when needed, whilst allowing continuity of care and minimal disturbance to daily life. It provides additional access to healthcare without over- burdening health care professionals. For users, the virtual care increases the feeling of being in control and is easy to use and understand. The ability to provide instantaneous feedback means a more effective evaluation of health care interventions is possible. The simple method of facilitating further discussion contributes to an increased participation in the care which means that any potential problems or obstacles are discovered more quickly. Vista Dialog complements the usual care at the outpatient clinic and other eHealth services.

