### Measures and data collection

All data will be collected in-person at the diabetes clinic (clinical variables and psychometric measures). Outcomes measurement will be completed at baseline, 6 months, 12 months, and after 18 months in the wait-list group (control group).

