## Discussion

The aim of this study is to evaluate the effect of a virtual diabetes clinic on treatment satisfaction, quality of life and glycaemic control in young adults (aged 18–25 years) with type-1 diabetes. We chose to include young adults because we want to see if participants using virtual diabetes care show improved: HbA1c levels; time in ranges for continuous subcutaneous glucose monitoring; quality of life; physical, mental and social health; and general treatment diabetes satisfaction. Time in range is the percentage of *time* that glucose levels are in low, target and high *ranges*. We will use Check Your Health Scale and treatment satisfaction assessed with the DTSQ, to detect changes in perceived health and general quality of life. The evaluation points for the intervention will be at baseline, and 6 and 12 months (virtual care) to allow comparisons and determine any changes.

In Sweden, all Patients with type 1 diabetes are treated at specialist centres, which means that all patients at the clinic who fulfil the inclusion criteria can be enrolled, regardless of race and ethnicity.

Data from national register in Sweden, include almost 90% of all diabetes patients. Data indicate that more than 70% of young patients with type 1 diabetes have a HbA_1_c level above the target level of 52 mmol/mol [27]. For this reason, it is important to take actions to support patients to attain optimal glycaemic control and at the same time maintain a good quality of life and to postpones diabetes-related complications.

The potential reduction of unsatisfactory glycaemic control and burden of diabetes using virtual diabetes care would be of benefit, and potentially even more clinically significant, in comparison with usual care (i.e. face-to face care meeting).

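### The only longitudinal analysis named is a within-group GEE over three unspecified visits, so its 12-month results cannot show the virtual clinic's effect

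*Protocol article*

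**What the plan says.** The protocol article (Statistical analysis and power calculation) names two analyses that matter here.

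- Main comparison: "The difference at the 6-month follow-up between the intervention and wait-list control groups (adjusted for values at baseline) will be analysed" with a two-sided t-test, by intention to treat.
- Longitudinal analysis: "Generalised estimating equation regression models will be used for comparisons within groups over the three time points". No group term or group-by-time term is given, and the months are not named.

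The schedule is in two other sections. Under Measures and data collection: "Outcomes measurement will be completed at baseline, 6 months, 12 months, and after 18 months in the wait-list group (control group". Under Intervention, "the wait-list control group will be offered the intervention after 6 months", and at that point "The intervention group will then continue with the intervention while the wait-list control group starts the intervention". The same section explains the last visit: "Finally, data at 18 months will be collected for the wait-list group (after having access to the virtual clinic for 12 months".

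The Discussion describes the assessment points in terms of exposure: "The evaluation points for the intervention will be at baseline, and 6 and 12 months (virtual care) to allow comparisons and determine any changes".

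The primary objective (Study aim) is to evaluate the effect of the virtual clinic.

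**The concern.** The article does not leave the longitudinal model open. It fixes the method (GEE), the contrast (within groups) and the number of visits (three). Two difficulties follow.

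First, the intervention arm has three visits but the wait-list arm has four, so the count does not identify the wait-list visits to be analysed. If the choice is left open, it could be made after the data are seen.

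Second, change within an arm is the sum of whatever the clinic does and whatever would have happened anyway. The GEE is the only analysis named that reaches month 12. If its results are used to say how the clinic performs over a year, they answer a different question from the stated objective. Separate within-arm tests also invite a reader to compare a significant change in one arm with a non-significant change in the other, which is not a test of the difference.

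**Working it through.** **1. The plan's own figure.** The article powers the 6-month comparison "To detect a mean difference of 6 mmol/mol (standard deviation [SD] = 9) in HbA1c", with two-sided alpha 0.05 and 80% power, and states 37 per group. Normal approximation: n = 2 × (1.960 + 0.842)² × 9² / 6² = 2 × 7.85 × 2.25 = 35.3, rounded up to 36. The t-based solution is 36.3, rounded up to 37, with power 80.8% at 37. The figure reproduces and is not in dispute.

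**2. Visits and exposure side by side** (Intervention; Measures and data collection).

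| Study month | Intervention arm | Wait-list arm |
|---|---|---|
| 0 | no access yet | no access yet |
| 6 | 6 months of access | 0 months of access |
| 12 | 12 months of access | 6 months of access |
| 18 | not scheduled | 12 months of access |

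There are two ways to obtain three points in the wait-list arm:

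- Study months 0, 6, 12: the series contains one interval without access and one with it, and month 18 is left out. Categorical months would keep the two intervals apart and a linear time term would pool them. The article does not say which applies.
- Months 6, 12, 18, aligned on access: the series leaves out months 0 to 6, the only follow-up without access in the trial and the only direct information on the shared time trend.

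**3. What each contrast estimates.** Let d be the change over months 0 to 6 that both arms share, and τ the effect of access. The intervention arm's change is d + τ and the wait-list arm's is d. The between-arm difference is τ, while the within-arm change in the intervention arm is d + τ. From month 6 both arms have access, so no analysis can give a randomised comparison with usual care alone. The month-12 difference compares 12 months of access with 6.

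**4. Illustration with no clinic effect (τ = 0).** From the article: SD 9, taken as the SD at one visit (the article does not say what it is the SD of), and 37 per arm. The upper n of 50 is half of the planned 100 at 1:1. Assumed: within-person correlation ρ of 0.5 to 0.8, and a shared fall d over 6 months.

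SE of the within-arm change = 9 × √(2(1 − ρ)/n).

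P(significant) = Φ(d/SE − 1.96) + Φ(−d/SE − 1.96).

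- Low end, n = 37, ρ = 0.5: SE = 9 × √(1/37) = 1.48. For d = 3, d/SE = 2.03 and P = 0.527.
- High end, n = 50, ρ = 0.8: SE = 9 × √(0.4/50) = 0.805. For d = 3, d/SE = 3.73 and P = 0.961.

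| Shared fall (mmol/mol) | n = 37, ρ = 0.5 | n = 50, ρ = 0.8 |
|---|---|---|
| 0 | 5% | 5% |
| 1 | 10% | 24% |
| 2 | 27% | 70% |
| 3 | 53% | 96% |

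If SD 9 is instead the SD of the change (the same as ρ = 0.5, since 9 × √(2 × 0.5) = 9), one-sample t-test power is 26.0% to 33.8% for a fall of 2 and 50.5% to 63.7% for a fall of 3, at n = 37 to 50.

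**5. Check with the GEE itself.** Simulation with exchangeable correlation, robust standard errors, ρ = 0.7, 50 per arm, 400 runs and no treatment effect. For shared falls of 0, 2 and 3 mmol/mol, the within-group 6-month contrast was significant in 6%, 50% and 84% of runs. The group-by-time contrast was significant in 7%, 6% and 4% (simulation error about 1 point around 5%).

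**The case against.** Much can be said for the plan.

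- A reader might infer that the trial gives up its randomised comparison. It does not. The baseline-adjusted 6-month test between arms is the main analysis, falls before the wait-list arm gains access, and uses that arm's months 0 to 6 as the comparator. This stands in full.
- The three points have a coherent reading: 0, 6 and 12 months of access in each arm. The Discussion's wording and the stated reason for month 18 point that way. So does the timing of the DTSQc (month 12 in the intervention arm, month 18 in the wait-list arm). This stands as a plausible reading, but the article never applies it to the GEE.
- A within-group test asks whether the mean changed. If HbA1c really falls by 3 mmol/mol, rejecting is correct, so the percentages above are power. They become error rates only if the change is attributed to the clinic. This also stands.
- No HbA1c entry threshold is set, so regression to the mean from selecting high values should be weaker than in a trial with one. Secular trend and participation effects remain.
- Model terms and time coding are often left to a full protocol or analysis plan, and neither is shown. That covers the missing detail, but not the stated choice of a within-group contrast.

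**Conclusion.** The point holds, confined to the supplementary longitudinal analysis. As stated, that analysis has no between-arm contrast and does not identify the wait-list visits it uses. Its 12-month results cannot separate the clinic from other causes of change. The randomised 6-month result and the sample size are untouched.

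A reader might also infer that the GEE p-values will be presented as proof of efficacy. The article does not say so. The Discussion ties the assessment points only to making comparisons and determining changes, so misreading is a foreseeable risk and not a stated intention.

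The size depends on assumptions the article does not supply: the shared fall, the correlation and the meaning of SD 9. With falls of 2 to 3 mmol/mol and the ranges used here, a within-arm change would be significant in roughly 27% to 96% of trials with no clinic effect, against about 5% for a between-arm contrast. Severity is minor to moderate.

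**What to change.** Replace the within-group GEE with one GEE or mixed model fitted to months 0, 6 and 12 from both arms, with month as a categorical factor, group-by-month terms and baseline constrained equal across arms. Then:

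- Report the month-6 contrast as the randomised effect of access against usual care, consistent with the primary analysis.
- Report the month-12 contrast as immediate against delayed access (12 against 6 months of access). A null result there would not show that the clinic has no effect.
- Report within-arm changes, including the wait-list arm's 6, 12 and 18-month series aligned on access, with confidence intervals and as descriptive, uncontrolled follow-up. Do not use them as evidence of effect.
- If a model-based 12-month effect of access is also wanted, state its assumption that immediate and delayed access have equal effects.

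Month 18 stays out of the joint model because only the wait-list arm is seen then. A categorical month-18 term would absorb that cell and add essentially nothing to the effect estimates.

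The cost is analysis wording only, with no new visits or data. The downside is that the 12-month results carry a weaker interpretation, without a usual-care control.
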